### Exploratory outcomes

We will collect exploratory outcomes data to test the feasibility of data collection; this trial is not designed to test hypotheses regarding efficacy. Exploratory outcomes including length of parent attendance of FCR, hospitalization of the infant, human milk feeding, frequency of medical error, parent-reported experience, parental activation (comfort with child’s care), and quality of life will be collected. Parent attendance of FCR will be measured from the date of participation until the date of discharge from the NICU. Parent FCR attendance is defined as the number of FCR attendance days either in person or with videoconferencing (numerator) divided by the infant’s total number of weekday round encounters (denominator).

Length of hospitalization of the infant will be measured as total days in the NICU, based on the midnight census, and will be measured through EHR review. Breastfeeding outcomes are defined as parents’ own human milk feeding and will include breastfeeding initiation or initiation of expression of parental human milk along with any and exclusive parental human milk at NICU discharge. Parental human milk feeding includes feeding directly from the breast/chest or receipt of parental human milk through another mechanism of delivery (such as syringe and bottle). We are defining exclusive human milk feeding as receipt of only parental human milk (with or without medically required fortification) and will be measured through EHR review.

Parent-reported outcomes will be collected via a survey packet. Parent experience will be measured through two items assessing overall experience from the Child Hospital Consumer Assessment of Healthcare Providers and Systems (HCAHPS) Survey [18, 19]. Parent activation, or a parent’s comfort with their child’s care, will be measured using the Parent-Patient Activation Measure (P-PAM) [20, 21]. Parental quality of life will be measured using the PedsQL™ Family Impact Module [22].

Medical errors and adverse events will be obtained via solicited reports and review of EHR data, using procedures as previously described in our prior vFCR pilot study [5].

### Implementation evaluation

#### RE-AIM mixed methods implementation evaluation

We will use the RE-AIM framework to conduct an implementation evaluation within this trial [15, 23]. Mixed methods with a convergent design [24] will be utilized to evaluate the vFCR intervention among LOE families.

#### Quantitative phase

Descriptive statistics will be used to describe the Reach, Effectiveness, Adoption, and Implementation Domains. We will use the existing Extended Care usage report to obtain data on vFCR encounters that use an interpreter during the 3 months after the trial ends (Maintenance). To characterize Reach and Adoption, we will report data by groups defined by infant, parent(s), and family characteristics. Imputation will not be used for missing data.

### Integration

We will use a convergent design [16] to integrate the quantitative and qualitative data. We will compare quantitative and qualitative data at qualitative analysis meetings to permit the opportunity to explore emerging findings in subsequent interviews. Data will be merged and categorized into the domains of the RE-AIM framework [15]. These converging data will allow us to refine our approach based on the integration results (see Table 3).

**Table 3 Tab3:** The use of RE-AIM for quantitative and qualitative phases

Dimension	Quantitative items	Qualitative items
Reach	% excluded and reasons Characteristics of LOE families who subscribe to use vFCR	Explore factors influencing reach Explore factors influencing subscription
Effectiveness	Heterogeneity of exploratory outcomes in subscribers	Explore mechanisms of potential heterogeneity effects Explore unmeasured effects of the intervention
Adoption	Subscriber use of vFCR	Explore factors influencing parent participation Explore factors influencing medical staff participation
Implementation	Use of professional interpreter in vFCR encounter % of vFCR encounters with technical issues	Explore factors impacting the use of medical interpreters Explore factors influencing implementation
Maintenance	Number of vFCR encounters with LOE families during the 3-months after the trial ends	Explore factors influencing sustainability

*vFCR* virtual family-centered rounds, *LOE* language preferred other than English

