### Participant outreach

A research coordinator will make three attempts to contact each eligible parent until they decline or accept the invitation to subscribe to vFCR. Subsequently, every 2 weeks, new invitations will be sent to those who initially declined participation in vFCR. We will repeat outreach every 14 days because we learned in our previous NICU vFCR pilot trial that sometimes parents decline and then change their decision and would appreciate continued outreach to subscribe to use vFCR throughout their child’s hospitalization [5].

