### Feasibility objective outcomes

We will test the feasibility of conducting a trial for vFCR in NICU patients with LOE parents. Feasibility will be assessed through the following objectives (Table 2):Objective 1 (primary feasibility objective) will measure the reach of vFCR for LOE families and will be met if at least 75% of enrolled families have at least one parent who subscribes to use vFCR.Objective 2 will monitor uptake of vFCR and will be met if at least 70% of enrolled families use vFCR at least once during their infant’s hospitalization. We will measure the percent of enrolled families that participate in vFCR by tracking logins to the ExtendedCare application that is used for parent-to-provider video access during vFCR.Objective 3 will measure the fidelity the intervention and will be met if at least 95% of vFCR with a parent in attendance whose language preference is other than English includes a professional medical interpreter in the parent’s preferred language.Objective 4 will measure the technical feasibility and will be met if at least 90% of vFCR encounters have no technical issues. This will be assessed using vFCR observations, parent solicited reports, and reviewing the hospital helpdesk technical issues log during the study period.Objective 5 will assess the feasibility of survey data collection with a goal of survey response rates being at least 75% and with missingness for each variable of interest being less than 10%.

**Table 2 Tab2:** Feasibility objectives

Objectives	Indicator	Criteria for success
*Feasibility* of reach of vFCR	At least one LOE parent subscribes to vFCR	Subscription of at least one parent to vFCR will be at least 75% among LOE-enrolled families
*Feasibility* of uptake of vFCR	Use of vFCR during the trial period	Parent use of vFCR at least once will occur among at least 70% of enrolled families
*Feasibility* of intervention fidelity	Interpreter use for vFCR encounters with a parent in attendance with LOE	Use of a professional interpreter will occur in at least 95% of vFCR encounters that have a LOE parent in attendance
*Feasibility* of technology	Technical issues	Among attempted vFCR encounters, at least 90% will have no technical issues
*Feasibility* of data collection	Survey response for survey-derived outcome	Survey response rate will be at least 75%; all data elements will have less than 10% missing values

*vFCR* virtual family-centered rounds, *LOE* language preferred other than English

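### The RE-AIM Effectiveness item covers subscribers only, and late subscription requires a longer stay, so length of stay can show apparent heterogeneity with no effect of vFCR

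*Protocol article*

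**What the plan says.** Table 3, under Integration, defines the quantitative content of the Effectiveness domain in one entry: "Heterogeneity of exploratory outcomes in subscribers". Its qualitative counterpart asks the interviews to look for mechanisms behind any such heterogeneity.

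Subscription follows enrolment and can come late. Participant outreach starts with up to three contact attempts per parent. After that, "every 2 weeks, new invitations will be sent to those who initially declined participation in vFCR". The stated reason is that "sometimes parents decline and then change their decision and would appreciate continued outreach to subscribe to use vFCR throughout their child’s hospitalization", so the protocol expects some late conversion, but it gives no rate.

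Under Exploratory outcomes, "Length of hospitalization of the infant will be measured as total days in the NICU, based on the midnight census". The count does not start at subscription. Attendance has its own window: "Parent attendance of FCR will be measured from the date of participation until the date of discharge from the NICU". Statistical methods uses weekdays as the offset for attendance and total stay as the offset for medical errors.

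Three statements limit the point. Study overview enrols every eligible family. Statistical methods reports exploratory estimates with 95% confidence intervals and does not confine them to subscribers. Exploratory outcomes says that the trial is not designed to test efficacy.

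**The concern.** Being a subscriber depends partly on one of the outcomes to be described. A family discharged within two weeks of its first refusal receives no further invitation, while a family whose infant stays 60 days can receive four. A subscribers-only summary therefore adds some long-stay families and leaves out the short-stay families who were equally reluctant.

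The consequence does not depend on an efficacy test, because it operates inside the subscriber group. Suppose a characteristic such as language, distance from the hospital or work goes with initial reluctance. Subscribers with that characteristic will include more late converters, and so will show longer stays. Table 3 would present this as heterogeneity, the interviews would be asked to explain it, and Integration lets emerging findings shape later interviews. The article's background expects telehealth rounds to shorten stay. This selection works the other way and could mask such a pattern.

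**Working it through.** **The protocol's own figures.** It gives no figure on this point. Its one computed figure is the error margin of at most 16.3 percentage points at n = 36. That reproduces as 1.96 × √(0.5 × 0.5 / 36) = 16.3 points, but nothing below depends on it.

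**Inputs from the protocol.** Re-invitation interval 14 days; stay counted as total NICU days; n = 36; Objective 1 is met if "at least 75% of enrolled families have at least one parent who subscribes to use vFCR".

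**Assumptions not in the protocol.** First invitation near admission; log-normal stay with median/mean of 10/20, 14/25 or 20/30 days, rounded up to whole days; acceptance p0 at the first invitation (0.40 to 0.75) and q at each re-invitation (0 to 0.3), neither depending on stay; no effect of vFCR on stay.

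**Model.** For a stay of L days the number of re-invitations is k = floor((L − 1)/14), and

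P(subscribe) = 1 − (1 − p0)(1 − q)^k.

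If q = 0 this equals p0 whatever the stay. If q > 0 it rises with L.

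**Results** (simulated, 2,000,000 stays per setting; mean stay in days):

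| Median/mean | p0 | q | Subscribing | Subscribers | Non-subscribers | All enrolled | Subscribers vs all |
|---|---|---|---|---|---|---|---|
| 14/25 | 0.70 | 0 | 70.0% | 25.5 | 25.5 | 25.5 | 0 |
| 14/25 | 0.75 | 0.1 | 77.7% | 27.2 | 19.7 | 25.5 | +6.5% |
| 14/25 | 0.70 | 0.2 | 75.6% | 28.4 | 16.7 | 25.5 | +11% |
| 14/25 | 0.50 | 0.2 | 59.3% | 31.6 | 16.7 | 25.5 | +24% |
| 20/30 | 0.75 | 0.1 | 78.4% | 32.1 | 24.8 | 30.5 | +5% |
| 10/20 | 0.70 | 0.3 | 75.6% | 23.3 | 11.8 | 20.5 | +14% |
| 10/20 | 0.40 | 0.3 | 51.3% | 28.8 | 11.8 | 20.5 | +40% |

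Over all settings with q > 0 the excess runs from about 5% to 40%. With p0 of at least 0.70 it runs from about 5% to 14%.

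**Where the excess comes from.** Take 14/25 days, p0 = 0.70, q = 0.2. Initial acceptors are 70.0% of families and average 25.5 days. Late converters are 75.6% − 70.0% = 5.6% of families and average about 64.5 days. The subscriber mean is (0.700 × 25.5 + 0.056 × 64.5) / 0.756 = 28.4 days. At n = 36 this is about 36 × 0.756 = 27 subscribers, of whom 36 × 0.056 = 2 are late converters, so two families account for the shift.

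**Apparent heterogeneity.** Take two groups of families with the same 14/25 stay distribution and q = 0.2, differing only in first acceptance, 0.75 against 0.50. Their subscriber means are 27.8 and 31.6 days. That gap of 3.8 days, or 14% (31.6 / 27.8 = 1.14), arises with no effect of vFCR and no true difference in stay.

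**The case against.** The best defence is that the item is descriptive, within subscribers, in a single-arm trial that disclaims efficacy testing. How outcomes vary among the families reached is a legitimate RE-AIM question. All-enrolled estimates are already available through Statistical methods, and the entry is one short cell in a condensed article. Much of this stands. It keeps the point minor and confines it to one domain. It does not remove the point, because the artefact appears in the within-subscriber description itself, and Table 3 asks the interviews to explain what is found there.

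A reader might infer more than the documents support:

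- *That outcome data on decliners are discarded.* They are not. Exploratory outcomes are neither collected nor estimated under a restriction to subscribers. Only the Effectiveness entry carries one.
- *That subscribers as a whole are selected by length of stay.* Only late converters are. With first acceptance of at least 70% they make up about 3% to 12% of subscribers under the assumptions above.
- *That the distortion is built in.* It needs at least some successful re-invitations, which the protocol expects but does not quantify.
- *That it is very large.* If every invitation had acceptance 0.4 and half the infants stayed 10 days and half 60, subscribers would average 44.9 days and non-subscribers 15.7. The arithmetic is right, but the protocol supports neither assumption. The implied subscription of 66% misses the 75% target, and the protocol plans no contrast between subscribers and non-subscribers.

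The offsets for attendance and errors, and the separate attendance window, lessen the link with stay for those outcomes. They do not remove it, since total stay still includes days before a late subscription.

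**Conclusion.** The point holds as a minor one. The Effectiveness item is defined on a group whose membership depends partly on length of stay, one of the outcomes it describes. The direction is certain if any re-invitation succeeds and acceptance does not itself fall with stay: subscribers then have longer stays than all enrolled families under no effect. The size is not determined by the protocol. Under the stated assumptions it is about 5% to 14% in mean stay when first acceptance is at least 70%, which is where the subscription target would roughly be met. It reaches about 40% when first acceptance is low, and it is zero without late conversion. The size was calculated for length of stay only. The protocol's main exploratory estimates are not affected. What is exposed is the RE-AIM Effectiveness domain and its integration with the interviews.

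**What to change.** Reword the Table 3 Effectiveness entry as: *exploratory outcomes and their heterogeneity in all enrolled families, with subscribers also shown separately by acceptance at the initial invitation versus at a re-invitation*. Add a sentence that length of stay among subscribers is not to be read as an effect of vFCR. Both parents of a family may be invited separately, so state how the family is classed when they respond at different times, for example by the first parent to subscribe.

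The cost is one table entry and a descriptive split. The outcomes are already planned for all enrolled families, and the date of subscription should be available from the research team logs. The drawback is small groups. At n = 36 and 75% subscription there are about 36 × 0.25 = 9 non-subscribers and only a few late subscribers, so the split can be descriptive only.

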### Participant timeline

We will conduct the feasibility study over a 12-month period. Participation in the study and the intervention delivery will occur in the first 12 months. The RE-AIM mixed methods evaluation will occur during the first and second year with the completion of data collection, analysis, and integration occurring in the second year.

### Sample size

The sample size of this feasibility study is calculated at *n* = 36. This sample size will allow us to estimate proportions in feasibility objectives 1, 2, and 5 with error margins ≤ 16.3 percentage points. Eligible participants will be approached by a research assistant during daytime hours on weekdays to reach the target sample size. Based on our previous pilot vFCR study at the same study site, we anticipate exceeding the sample size goal and enrolling up to 45 participants during the enrollment period [5].

### Data collection

Data collection will be ongoing and include daily weekday vFCR observations, parent surveys, and reviews of the EHR and technical issues log. Adherence to the feasibility objectives will be monitored. For objective 1, we will use daily chart review to track the number of LOE-eligible infants indicated by preferred language in the infant chart and calculate the percentage subscribed based on this total number. If the preferred language is not listed, research coordinators will cross-reference notes in the medical record for admitted patients in the NICU to determine the language preferences of the family. For objective 2, we will track logging in to the ExtendedCare application for subscribed families to determine the percentage that access the technology. Encounters will be measured using a dichotomous rating among the vFCR encounters with a LOE parent(s) in attendance of whether the FCR encounter includes the presence of the professional medical interpreter for objective 3. Objective 4 will be assessed using FCR observations, parent-solicited reports, and helpdesk technical issues log. Objective 5 will be assessed by survey response rates and by missing data elements for each variable of interest.

Data collection for exploratory outcomes will be collected primarily through several methods. FCR parent attendance is collected by the NICU rounding team during weekday rounds where a data collection sheet is marked if a parent joins FCR. EHR review will be used at discharge to measure length of stay and any human milk feeding. Medical errors and adverse events will be reviewed by comparing EHR data with the study site’s internal incident reporting system along with solicited reports, as previously described in the vFCR pilot study [5].

Exploratory outcomes of parent experience, parental activation, and parent quality of life will be measured at hospitalization discharge through a survey packet. Surveys will be administered to one parent per enrolled family; this parent will be the parent with a language preference other than English. For families with more than one parent with a language preference other than English, the family will select which parent will complete the survey packet. Survey packets will be translated into the six most spoken languages among parents of infants in our NICU (Spanish, Russian, Pashto, Arabic, Farsi, Punjabi). For parents with a preferred language other than these six languages for whom we will not have prepared language-appropriate packets, we will administer the surveys verbally using a professional interpreter. Surveys will be distributed at the time of NICU discharge. Non-respondents will be followed up 7 days after discharge. If surveys are not returned by 21 days post discharge, the survey will be considered a non-response.

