### Setting and population

This study will take place in a 121-bed children’s hospital within a large academic medical center in Northern California, USA. This hospital NICU has 49 beds and accepts patients from over 33 counties from a 65,000-mile region that includes Northern California, Southern Oregon, and Nevada.

Family units will be included in this trial and are defined as the hospitalized infant(s) and their parent(s) or guardian(s). Eligible families will have an infant who is < 365 days of age admitted to the NICU and at least one adult (aged 18 years or older) parent with a preferred language that is other than English. Exclusion criteria are families with restrictions placed by child protective services (such as restricted access to patient information or limited visitation), families previously enrolled in this trial on a prior NICU admission, and/or families already enrolled in a different trial that includes a FCR intervention.

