### Study overview

This single-arm feasibility trial will assess the use of vFCR for LOE families with hospitalized infants in the NICU. Over a 12-month study period, we will conduct the quantitative phase and enroll all eligible family units, allowing accurate measurement of denominator values for feasibility objectives. Beginning in the first year and continuing into the second year of the study, we will conduct the qualitative phase and mixed methods evaluation.

We will invite the parents of enrolled family units to subscribe to use vFCR, by providing their contact information (i.e., cell phone number or email) to receive a secure link to join vFCR each weekday morning, excluding university holidays. In this way, subscribed parents have the option to participate in rounds via vFCR with video medical interpreting services or through usual care. Usual care is defined as attending FCR at bedside with a medical interpreter available or no participation in rounds. If family units have more than one parent listed in the electronic health record (EHR), both parents will be separately invited to subscribe to vFCR.

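### Objective 1 is judged per family, but Data collection calculates it on the number of eligible infants; near 75% the two can give different verdicts

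*Protocol article*

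**What the plan says.** All references are to the Protocol article.

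- **Criterion.** Feasibility objective outcomes says that Objective 1, the primary feasibility objective, "will be met if at least 75% of enrolled families have at least one parent who subscribes to use vFCR". Table 2 repeats the family as the unit: "Subscription of at least one parent to vFCR will be at least 75% among LOE-enrolled families".
- **Calculation.** Data collection says that, for Objective 1, daily chart review will be used to "track the number of LOE-eligible infants indicated by preferred language in the infant chart and calculate the percentage subscribed based on this total number".
- **Unit of inclusion.** Under Setting and population, family units "are defined as the hospitalized infant(s) and their parent(s) or guardian(s"). Siblings admitted together are therefore one family unit but two or more infants.
- **Enrolment.** Study overview plans to "enroll all eligible family units, allowing accurate measurement of denominator values for feasibility objectives".

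No sentence says that siblings are reduced to one record before the Objective 1 percentage is taken.

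**The concern.** The criterion has families as its denominator and the calculation rule has infants. The two counts differ whenever one eligible family has more than one infant in the unit. An infant-based percentage weights each family by its number of infants. It matches the family-level percentage in expectation only if having multiples is unrelated to subscribing, and in a given sample only if multiples are spread in proportion between subscribing and non-subscribing families.

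The numerator is also open. Parents subscribe, not infants, so a percentage taken on infants could mean infants of subscribing families over all infants, or subscribing families over all infants. The second mixes units and can only be too low.

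At stake is the met/not-met verdict on the primary objective, which is a fixed cut at 75%. A coordinator who followed Data collection to the letter would report a number that is not the one the criterion names.

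**Working it through.** **Inputs.** Threshold 75% of enrolled families (Feasibility objective outcomes). Sample size 36, anticipated enrolment up to 45, stated margin at most 16.3 points (Sample size). 95% Wilson intervals (Statistical methods). The share of families with multiples is not given; the twin counts below are assumptions.

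**The plan's own figure.** Half-width at p = 0.5, n = 36: 1.96 × √(0.5 × 0.5 / 36) = 0.163, or 16.3 points. This reproduces. The Wilson half-width at 18/36 is 15.5 points, so the stated bound also holds for the planned interval.

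**Three candidate percentages.** Let N be families, S subscribing families, t twin pairs in all, and a the twin pairs in subscribing families.

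- Family-based (the stated criterion): S / N
- Infant-based in both places: (S + a) / (N + t)
- Mixed, families over infants: S / (N + t)

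On the family basis the criterion needs 27/36 = 75.0%, or 34/45 = 75.6%.

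**Infant-based, examples near the threshold.**

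| N | S | Family-based | Twin pairs assumed | Infant-based |
|---|---|---|---|---|
| 36 | 27 | 75.0%, met | 1, non-subscribing | 27/37 = 73.0%, not met |
| 36 | 28 | 77.8%, met | 2, non-subscribing | 28/38 = 73.7%, not met |
| 36 | 26 | 72.2%, not met | 4, subscribing | (26+4)/(36+4) = 30/40 = 75.0%, met |
| 45 | 34 | 75.6%, met | 1, non-subscribing | 34/46 = 73.9%, not met |
| 45 | 33 | 73.3%, not met | 3, subscribing | (33+3)/(45+3) = 36/48 = 75.0%, met |

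**Mixed units.** Here the location of the twins does not matter. With S = 30 of 36, 83.3% falls to 30/41 = 73.2% with any five twin pairs.

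**How often the verdict would differ.** In a simulation with 36 or 45 families, true subscription of 70% to 85%, 5% to 20% of families with twins, and twin status independent of subscription (25,000 runs per setting), the verdict differed from the family-based one in about 1% to 10% of runs with infants in both places. With mixed units it differed in about 11% to 74%. All of these ranges are assumed.

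**The case against.** The strongest reply is that Data collection describes case-finding and nothing more. Preferred language is recorded in the infant's chart, so infants are what the coordinator screens. The next sentence there refers to the family's language preference, and Objective 2 in the same paragraph is counted in subscribed families. The criterion is stated per family twice, and inclusion and enrolment are by family unit. On this reading the team would count families in practice. That is plausible, so a reader should not infer that multiples certainly will be double-counted. What stands is that the sentence does more than name a data source: it says which total the percentage is based on, and that total is infants.

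A second reply is size. If infants are used consistently and twins are unrelated to subscription, a changed verdict is uncommon. The intervals also hardly move: 26/36 has a Wilson interval of 56.0% to 84.2%, and 30/40 has 59.8% to 85.8%. This is fair as to estimation, but the objective is declared met or not met at a fixed cut. The larger simulated risk belongs to the mixed ratio, which the article does not state; it merely leaves it open.

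Two stronger readings are tempting and not supported:

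- **A third denominator.** Sample size says "Eligible participants will be approached by a research assistant during daytime hours on weekdays to reach the target sample size". One might infer that only families approached on weekdays count. The sentence defines no denominator, Study overview enrols every eligible family unit, and Participant outreach ties contact attempts to the invitation to subscribe. The 36 and 45 are a calculated sample size and an anticipated enrolment, not counts of approached and eligible families.
- **A faulty precision statement.** The 16.3-point margin reproduces and is not in error.

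**Conclusion.** The point holds as a contradiction between the criterion and its calculation rule. Taken literally, Data collection yields an infant-based percentage that does not estimate the family-level criterion for the primary objective. The difference matters near 75%, where one twin pair can be enough to move a met result to not met (75.0% to 73.0%), and four pairs can move a result the other way (72.2% to 75.0%). Away from the threshold, consistent infant counting would rarely alter the verdict; dividing families by infants could do so from further off, and always downward. These sizes rest on assumed twin counts, since the article gives no multiple-birth rate. Because the conflict sits in the rule for the primary objective, it should be removed before the percentage is calculated.

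**What to change.** In Data collection, state for Objective 1 that:

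1. eligible infants found by daily chart review are collapsed to family units, each counted once however many infants it has;
2. the denominator is all enrolled family units, which under Study overview means all eligible ones;
3. the numerator is those family units with at least one subscribing parent, as the criterion already says.

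The numerator should not be narrowed in passing. The criterion in the text and in Table 2's success column says at least one parent, while Table 2's indicator column says an LOE parent. If the narrower form is intended, it should be stated openly in all places.

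The cost is a sentence or two of wording and a family identifier on the screening log. No further families or data items are needed, and the sample size is unaffected.
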